## Abstract

**Objective:**

Repetitive Transcranial Magnetic Stimulation (rTMS) has been used in cognition impairment due to various neuropsychiatric disorders. However, its optimum parameters and the neuroimaging mechanism are still of uncertainty. In order to simulate a study setting as close to real world as possible, the present study introduces a new orthogonally-designed protocol, consisting of the rTMS intervention with four key parameters (stimulating site, frequency, intensity and pulse number) and three different levels in each one, and aims to investigate the optimum parameters and the brain activity and connectivity in default mode network (DMN), dorsal attention network (DAN), central executive network (CEN) following rTMS intervention to post-stroke cognition impairment (PSCI).

**Methods:**

A single-center, orthogonally-designed, triple-blind randomized controlled trial will be conducted and forty-five PSCI patients will be recruited and randomly assigned to one of nine active rTMS groups based on four rTMS paraments: stimulating site, frequency, intensity and pulse number. Neuropsychological, activities of daily living, quality of life and functional magnetic resonance imaging (fMRI) evaluations were be performed pre-, post- and 3 months after rTMS.

**Discussion:**

This study evaluates the optimum parameters of rTMS for patients with post-stroke cognition impairment and explores the alteration of neural function in DMN, DAN, CEN brain network. These results would facilitate the standardized application of rTMS in cognition impairment rehabilitation.

## Introduction

Post-stroke cognitive impairment (PSCI) is one of the vascular cognitive impairments and probably develop into dementia [1]. It was reported that 20–70% stroke survivor suffered from the cognitive impairment within 6 months after stroke attack [2, 3]. It is not only a common, important disability after stroke but also could hinder the rehabilitation of stroke-related sequelae including motor dysfunction, sensor deficits and the limited activities of daily living [4]. The pathogenesis of PSCI is multifactorial being similar with VCI. In terms of brain structure, it is generally related to focal, multifocal or diffuse cortical and/or subcortical large infarct, microinfarcts or lacunes, as which is often affected important brain areas (thalamus, frontobasal and/or limbic systems, etc.) [5]. Functionally, the PSCI is due to the disfunction of neuronal metabolism, activation and connectivity, while the exact mechanism between vascular lesion, cognition, and neuroplasticity are not completely understood [6]. Current research shows that many non-invasive neuromodulatory techniques could improve cognitive impairment via neuroplasticity [7]. As a non-invasive brain stimulation,the repetitive transcranial magnetic stimulation (rTMS) was widely used as a primary or an add-on treatment to improve cognitive function in patients with stroke [8]. Several meta-analyses confirmed its promising and positive effect on PSCI [9–11]. In these studies, mostly rTMS schemes included four primary parameters: stimulating site, frequency, intensity and pulse number, however, the rTMS intervention scheme varied substantially and the considerable heterogeneities of rTMS parameters were the great challenging in its clinical practice. Furthermore, although accumulating studies have shown that rTMS could improve the cognitive function in many neurological and psychological diseases [12, 13], the brain functional mechanism is still unclear. The present study hypothesized that rTMS could promote the cognition recovery with an optimal parameter combination and it might be objectively existed that the interaction effects between the four parameters: stimulating site, frequency, intensity and pulse number. Furthermore, we predicted that the mechanism of rTMS might be related with the neuroplasticity in three brain networks: default mode network (DMN), dorsal attention network (DAN), central executive network (CEN). Hence, the prospective, single-center, orthogonally-designed, triple-blind randomized controlled trial will be conducted and will be aimed to explore the rTMS optimum parameters regimen for PSCI based on stimulating site, frequency, intensity and pulse number and the neuroimaging mechanism in default mode network (DMN), dorsal attention network (DAN), central executive network, (CEN) following rTMS treatment in PSCI patients. All participants will be assigned averagely to one of nine paralleled active rTMS groups which are designed according to the L_9_(3^4^) orthogonal array with four different parameters: stimulating site, frequency, intensity and pulse number. This trial protocol will be written in adherence to the standard protocol items: recommendations for interventional trials (SPIRIT) 2013 guidelines [14].

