#### (4) Sample size

Because no previous orthogonally designed study provides a significant difference of MoCA or MMSE scores for rTMS treatment to PSCI, which would allow us to accurately estimate the adequate sample size for this trial, we decided to recruit 45 PSCI patients who will be randomly divided into nine groups and three subgroups based on orthogonal design (5 patients per group, 15 patients per stimulating site subgroup), in consideration of the research grant, the recruitment feasibility and the recommended sample size in neuroimaging research (medians:14.5) [17].

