### 2. Interventions

#### (1) rTMS protocol

The rTMS treatments were delivered by a magnetic simulator (YRD CCY-I, YIRUIDE medical equipment co., LTD, Wuhan, China) with a figure-8 coil. The rTMS protocol was designed as nine combinations of four parameters at three different levels in each parameter: stimulating site (the dorsolateral prefrontal cortex, DLPFC, Brodmann areas 9 and 46; the inferior frontal gyrus, IFG, Brodmann areas 44 and 45; the temporo-parietal cortex, TPC, Brodmann areas 39 and 40), frequency (5Hz, 10Hz, 20Hz), intensity (90%, 100%, 110% of the resting motion threshold, RMT) and pulse number (1000, 1500, 2000), the detailed information are showed in Tables 1 and 2. The aforementioned rTMS parameters and different levels were predetermined based on the previous studies involving in rTMS treatment to cognition impairment duo to various neurological and psychological diseases. Once the PSCI patients were recruited, they were randomly allocated into one of nine active rTMS groups, a total of 20 sessions (four weeks, five consecutive daily sessions and two days of rest per week) active rTMS treatments with different parameters combination will be administered by two therapists with more than 5 work experience at the neuromodulating center of the rehabilitation medicine department, West China Hospital, Sichuan University. In order to improve the patient’s adherence to the intervention protocols, once every rTMS session was completed, a predesigned treatment record card should be filled and signed by the rTMS therapists and the patients or their authorized persons and ultimately returned to the study researchers.

**Table 1 pone.0271283.t001:** The orthogonal experimental factors and levels of rTMS.

Level	Experimental factor			
	A (Site)	B (Frequency, Hz)	C (Intensity, %RMT)	D (Pulse)
1	DLPFC	5	90	1000
2	IFG	10	100	1500
3	TPC	20	110	2000

Note: DLPFC: Dorsolateral prefrontal cortex; IFG: Inferior frontal gyrus; RMT: Resting motor threshold; rTMS: Repetitive transcranial magnetic stimulation; TPC: Temporoparietal cortex

**Table 2 pone.0271283.t002:** The orthogonal array L9(34).

Groups	Site (A)	Frequency (B)	Intensity (C)	Pulse (D)	rTMS protocols	Sample Size
1	TPC	5 Hz	100%RMT	1500	A_3_B_1_C_2_D_2_	5
2	IFG	20 Hz	100%RMT	1000	A_2_B_3_C_2_D_1_	5
3	IFG	10 Hz	90%RMT	1500	A_2_B_2_C_1_D_2_	5
4	TPC	10 Hz	110%RMT	1000	A_3_B_2_C_3_D_1_	5
5	DLPFC	5 Hz	90%RMT	1000	A_1_B_1_C_1_D_1_	5
6	IFG	5 Hz	110%RMT	2000	A_2_B_1_C_3_D_3_	5

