### 4. Statistical analyses

The data of MoCA-BJ, TMT, MBI, LIADL and SS-QOL were shown as mean ± standard deviation (SD) and analyzed by the range analysis and one-way analysis of variance (ANOVA), which was used the SPSS 22.0 software (IBM, Armonk, NY, USA, 2020). The range analysis was used to determine the influence of each parameter at a specific level on the effect indicator and obtain the optimum combination of rTMS parameters. The one-way ANOVA was used to determine the statistical significance in nine different parameters’ combination of rTMS. P < 0.05 was considered significant.

For ALFF and FC maps, paired T-test will be used for intra-group comparison and one-way ANOVA analysis will be used for inter-group comparison in the three stimulating site subgroups. Then multiple comparison correction will be performed using Gaussian random field theory (GRF) with voxel *p* < 0.005, cluster *p* < 0.05. The Pearson correlation analyses were used to calculate the correlations between the changes in ALFF and FC with the clinical symptom scores at baseline and the end of the rTMS treatment (*p* < 0.05).

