## Discussion

As a non-invasive brain stimulation technique, the rTMS uses high intensity magnetic field pulses to modulate neural activity and in turn modifying the brain function. Over the past few decades, rTMS is widely applied into the cognition impairment due to many neurological, psychiatrical and psychological diseases, such as stroke, Alzheimer’s disease, Parkinson’s disease, schizophrenia, obsessive compulsive disorder. Several meta-analyses and RCT have showed that the safe and beneficial value of rTMS in cognitive function rehabilitation [10, 33–35]. Given the more and more application of this method in clinical and research settings, it is crucial to understand what is the optimal parameters of rTMS for cognition impairment and how the rTMS modulates brain function via the high intensity magnetic field pulses. Fortunately, some researchers have realized these two key points. Beynel L et al. thought that the rTMS parameters include a vast composition of spatial and temporal parameters: coil geometry, stimulation target, stimulation intensity; pulse waveform, pulse train frequency, number of pulses, etc [36]. while it does not be summed precisely from the perspective of clinical application. Based on the previous literature related to multiple sessions of rTMS for cognition impairment, we hold the opinion that the most important four parameters of rTMS are stimulating site, stimulating frequency, stimulating intensity and pulse number. Orthogonal design is a powerful method for comparative effectiveness research, especially for intervention with multiple parameters, it could significantly reduce the experiment numbers and alleviate the research workloads [37]. In rehabilitation medicine, many physical modalities are delivered with a specific equipment by presetting several parameters in the meantime. It is important that these parameters should be investigated at the same time when we are going to assess the efficacy and safety of this intervention. For example, the rTMS will be delivered to a patient with cognition impairment, the stimulating site, frequency, intensity and pulses should be predetermined meanwhile. However, in the previous studies, it was common that only one parameter, such as frequency, be compared with different level, or be compared between active and sham rTMS. It is not entirely and exactly consistent with clinical practice. Hence, in order to investigate the optimum parameters of clinical value of rTMS for post-stroke cognition impairment, the present study is designed orthogonally with L_9_(3^4^) orthogonal array based four parameters with three different level in each parameter (sites: DLPFC, IFG, TPC; frequency: 5Hz, 10Hz, 20Hz; intensity: 90%RMT, 100%RMT, 110%RMT; pulse number: 1000 pulses, 1500 pulses, 2000 pulses). On the other hand, although many studies showed that the modulatory effect of rTMS on brain function, ig. enhancing the neural activity and the connectivity between different brain regions [38], is correlated to the improvement of cognition function [39], the exact neurological mechanism has not been understanded very well. Giacomo Koch et al. showed that the rTMS stimulation on precuneus enhances memory and neural activity and connectivity in default mode network [40]. Recep A Ozdemir et al. Showed that the default mode network (DMN) and the dorsal attention network brain network (DMN/DAN) specificity of rTMS activations is correlated with cognitive performance in healthy volunteers [41]. Reza Kazemi et al. showed that the bilateral rTMS stimulation on DLPFC changes resting state in CEN, DMN brain networks and cognitive function in patients with bipolar depression [42]. However, whether the brain networks related to attention and executive function (CEN, DMN, DAN) is enhanced activity and connectivity and is correlated with the cognitive improvement following the rTMS stimulation in patients with post-stroke cognition impairment are still unclear. Therefor, in the current study, the amplitude of low-frequency fluctuation (ALFF) and the functional connectivity (FC) of the resting-state fMRI signal has been adopted to reflect the regional brain network (CEN, DMN, DAN) activity and connectivity and further our understanding of the complex cognitive function recovery process underlying metaplasticity with rTMS, demonstrate how the adaptive metaplasticity can contribute to the cognition impairment, and show that whether the maladaptive metaplasticity play a role in the cognitive pathophysiology [43].

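### Interactions are hypothesised, but the saturated L9(3^4) array cannot estimate any, so the optimum combination from the range analysis is identified only if the four parameters act additively

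*Protocol article*

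**What the plan says.** The Introduction of the protocol article joins two ideas in one hypothesis. The first is benefit at a best setting: "The present study hypothesized that rTMS could promote the cognition recovery with an optimal parameter combination". The second concerns interactions: "it might be objectively existed that the interaction effects between the four parameters: stimulating site, frequency, intensity and pulse number". The same section says that the groups are "designed according to the L_9_(3^4^) orthogonal array with four different parameters", and the section on the rTMS protocol describes "nine combinations of four parameters at three different levels in each parameter". Table 2 leaves no column of the array empty.

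The sample size section gives "5 patients per group, 15 patients per stimulating site subgroup", 45 in total, chosen "in consideration of the research grant, the recruitment feasibility and the recommended sample size in neuroimaging research". There is no power calculation.

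The section on statistical analyses names two methods for the clinical outcomes. Range analysis is to show the influence of each parameter and "obtain the optimum combination of rTMS parameters". A one-way ANOVA compares the nine combinations at P < 0.05. Additivity is not stated as an assumption. The limitations in the Discussion mention the small sample, the single centre, the simple choice of levels and differing oral medication, but not that interactions are confounded with main effects.

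**The concern.** Range analysis takes one parameter at a time. It averages the outcome at each level over whatever the other parameters happen to be, picks the best level, and joins the four best levels into one regimen. That regimen is the best of all 81 possible combinations if the effects of the four parameters simply add. If they interact, the level means mix a parameter's own effect with interactions among the others.

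The protocol thus proposes that interactions may exist and then names its optimum by a method whose justification needs them to be absent or negligible. At stake is the trial's main product: the ranking of the four parameters and the recommended combination. Neither a different analysis of these nine cells nor more patients per cell can separate what the array confounds, so this is not a matter that a statistical analysis plan could settle.

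**Working it through.** **Inputs.** Four parameters at three levels, nine cells, 5 patients per cell (Tables 1 and 2; sample size section).

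**The plan's own figure.** 9 × 5 = 45 and 3 × 15 = 45, as stated. Without power inputs there is nothing further to reproduce.

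**Degrees of freedom.**
- Main effects: 4 × (3 − 1) = 8. Between nine cells: 9 − 1 = 8. Nothing is left over.
- The six two-factor interactions need 6 × 4 = 24 more. With the intercept, 1 + 8 + 24 = 33 parameters, against at most 9 estimable from nine cells.
- The 45 − 9 = 36 within-cell degrees of freedom estimate error. They allow the four columns to be tested but do not separate main effects from interactions.

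**Rank check.** Coding the nine rows of Table 2, the intercept plus four main effects has rank 9. Adding any of the six two-factor interactions leaves it at 9. Each interaction lies wholly in the main-effect columns of the other two parameters and not at all in those of its own two. The reason is visible in Table 2: every site–frequency pair occurs once, so the pair fixes both intensity and pulse number. The 4 degrees of freedom of site × frequency are the 2 of intensity plus the 2 of pulse number.

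The group list printed after Table 2 gives different combinations for groups 2, 3, 4, 7, 8 and 9. The two must be reconciled. The list is also orthogonal and saturated, so the conclusion holds under either; only which main effect absorbs which part of an interaction changes.

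**Illustrations on Table 2, without noise. All effect sizes are assumed.**

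1. *Wrong attribution, right optimum.* Only DLPFC with 10 Hz has a benefit, +3. It occurs in one cell (group 7), so each level in that cell has mean 3/3 = 1 and all other level means are 0. All four parameters show a range of 1.0, although intensity and pulse number do nothing. The combination picked is group 7, which is tested and truly among the best.

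2. *False main effect.* A pure site × frequency interaction gives +2 in groups 3, 5 and 8 and −1 elsewhere. Those three groups share 90% RMT, so the intensity means are 2, −1, −1, while site, frequency and pulse number all show 0, 0, 0.

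3. *Wrong optimum.* IFG/20 Hz +3, TPC/5 Hz +2, TPC/10 Hz +2, all else 0; these fall in groups 2, 1 and 4.
   - Site: DLPFC 0, IFG 3/3 = 1, TPC 4/3 = 1.33; range 1.33.
   - Frequency: 5 Hz 2/3, 10 Hz 2/3, 20 Hz 3/3 = 1; range 0.33.
   - Intensity: 90% 0, 100% 5/3 = 1.67, 110% 2/3; range 1.67.
   - Pulses: 1000 5/3 = 1.67, 1500 2/3, 2000 0; range 1.67.

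   The pick is TPC, 20 Hz, 100% RMT, 1000 pulses. Its true benefit is 0, it is not in Table 2, and the two inert parameters have the largest ranges.

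**How often.** In noise-free simulation (4,000 runs each, Table 2), range analysis found the true best of 81 as follows. The ratio is the assumed interaction SD to main-effect SD.

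| Ratio | Site × frequency only | All six interactions |
|---|---|---|
| 0 | 100% | 100% |
| 0.25 | 72% | 45% |
| 0.5 | 54% | 22% |
| 1 | 32% | 10% |

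**Precision of a predicted combination.** With outcome variance σ², each level effect has variance σ²/15 − σ²/45 = 2σ²/45. The grand mean plus four such effects has variance (1 + 4 × 2)σ²/45 = σ²/5, the same as an observed cell mean of 5 patients. The width of an interval for an untested combination therefore gives no warning that it is an extrapolation.

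**The case against.** Several points on the other side have force.

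- *The optimum need not be wrong.* A reader might infer that the named optimum fails whenever interactions exist. The design does not support that. If the only benefit is a synergy between one pair of levels, range analysis always recovers that pair (6 × 9 = 54 possible cases), because every level pair occurs exactly once; illustration 1 is such a case. With small interactions it also often picks correctly. This stands: the optimum is not identified, which is different from being false.
- *A valid analysis remains.* The one-way ANOVA compares the nine regimens with no assumption about additivity. This also stands. What is lost is attribution to single parameters and prediction for the 81 − 9 = 72 untested combinations.
- *Extrapolating beyond the tested cells is what orthogonal arrays are for,* and the Discussion gives fewer experiments as the reason for choosing one. True, but the justification is additivity, which should be declared, the more so where interactions are hypothesised.
- *The wording is tentative and the aim exploratory,* and no interaction test is promised. That softens the conflict but leaves the optimum resting on an unstated assumption.
- *All arms are active.* A reader might infer that the trial can say nothing about rTMS effects. That goes too far: a randomised difference between active regimens would show that the settings matter. Only absolute benefit over natural recovery or retest gain is out of reach.

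**Conclusion.** The point holds in this form: the hypothesised interactions cannot be estimated in this design, and both the parameter ranking and the optimum from the range analysis are identified only under additivity. The aliasing is exact. It depends on no assumption about sample size, SD or alpha, and it holds for Table 2 and for the group list alike.

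The size of the harm is not known from the document. It depends on how large the interactions are; the illustrations and simulated rates rest on assumed values and ignore sampling error. They show that the harm can range from misattribution with a correct optimum to an untested optimum with no benefit. They do not show that the trial's optimum will be wrong, nor that the comparison of the nine regimens is compromised.

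**What to change.** Recruitment is under way, so the remedy lies in wording and reporting:

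- Keep the remark that interactions are plausible, and state that this design cannot test them. Deleting it would not make additivity true.
- In the statistical analyses, declare that the range analysis assumes additive effects and that each two-factor interaction is aliased with the main effects of the other two parameters. Repeat this among the limitations.
- Limit parameter-level conclusions to a ranking of levels under additivity among active settings. Make no claim of absolute benefit of rTMS over natural recovery.
- If the predicted optimum is not one of the nine tested cells, report it as an untested prediction, with a confidence interval labelled as conditional on additivity.
- Report beside it the best tested cell with its confidence interval, noting that choosing the best of nine cells of 5 patients biases that estimate upward.
- Keep the one-way ANOVA as the comparison that needs no additivity.

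Cost: no new patients, arms or assessments. The price is a more modest claim about the optimum combination.

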
## Methods

### 1. Patients

#### (1) Study setting

This study will be carried out at the West China Hospital of Sichuan University (Chengdu, China). The post-stroke cognitive impairment patients in the wards of the departments of neurology and rehabilitation medicine from December 2021 to December 2023 will be screened for eligibility and finally 45 patients will be enrolled in this trial.

#### (2) Eligibility criteria

The study researchers will execute the eligibility screen in accordance with the inclusion and exclusion criteria. All the participants should sign an informed consent after eligibility confirmation.

Inclusion criteria:

Male or female patients between 18 and 75 years of age;Right-handed;Patients who meet the diagnostic criteria for vascular cognitive impairment reported in the Guidelines from the Vascular Impairment of Cognition Classification Consensus Study [15] and the Chinese vascular cognitive impairment guideline 2019 [16] as which mainly be concluded as: (1) Cognitive impairment at least one domain in attention and executive, memory, language and visuospatial function confirmed by clinical and neuropsychological evaluation (MoCA ≤ 24) with or without the impairment in instrumental activities of daily life (IADL); (2) Imaging evidence due to stroke confirmed by magnetic resonance imaging (MRI); (3) Cognitive impairment should be independent of the motor/sensory sequelae of the vascular event and with a clear temporal relationship (within 6 months and lasted for at least 3 months) between a vascular event and onset of cognitive deficits;No severe aphasia (Unable to accomplish cognitive tests);Normal cognitive functions before stroke;Voluntary participation and signed the informed consent (Signed by the patient or the authorized person).

Exclusion criteria:

Cognitive impairment due to primary or secondary neurological disease, such as normal cranial pressure hydrocephalus, frontotemporal dementia, Parkinson’s disease, multiple sclerosis, encephalitis and delirium;Cognitive impairment due to depression, schizophrenia, bipolar disorder, psychotic disorder, vitamin D deficiency, toxicosis or else systematic diseases;Drug/alcohol abuse/dependence within the last 3 months of first recognition of impairment.rTMS treatment contraindications such as epilepsy patients, pregnant or lactating women or with a metal or electric implanted device (eg. deep brain stimulator, ventriculoperitoneal shunt, aneurysm clip, pacemaker, cochlear, surgical staples on the scalp).MRI contraindications (such as metal implants or claustrophobia)participating in a concurrent pharmacological or nonpharmacologic treatment research.

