#### (5) Recruitment

This trial aims to recruit 45 in- or outpatients with PSCI in the West China Hospital of Sichuan University who are recommended by the rehabilitation physicians, therapists, or any other medical practitioners and willing to receive rTMS treatment. Once the oral consent to take part in the study is confirmed, written and verbal information about the study aim and procedures is provided to all the volunteer participants. There are no biological specimens collecting for storage and anticipated harm for the participants throughout the study. All the personal information and any other data about the potential or enrolled patients will be traceable in the medical records and available from the corresponding author on request in order to protect confidentiality. After the written informed consents are obtained from the eligibility-screened participants, the study will commence with the baseline assessment and then the randomized allocation.

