#### (6) Randomization and blinding

The random numbers sequence is generated using SPSS software in computer and all eligible patients were equal assigned to one of nine active rTMS treatment group based on four rTMS parameters. The random allocation and detailed rTMS protocol are only known by the rTMS physiotherapists and blinded to physicians, patients and other researchers (such as outcome assessors, data analysts). The rTMS physiotherapists are not involved in any other study work such as patient recruitment, randomization, allocation, outcome assessment and data analysis.

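### Time since stroke at entry is not clearly bounded and is not used in the analysis; a pre-specified model with baseline score and log time since stroke would bring a modest gain at little cost

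*Protocol article*

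**What the plan says.** **Entry window.** Methods 1(2), Eligibility criteria, requires the impairment to be independent of motor and sensory sequelae and "with a clear temporal relationship (within 6 months and lasted for at least 3 months) between a vascular event and onset of cognitive deficits". No other criterion refers to time since the stroke.

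**Setting.** Methods 1(1), Study setting, says that "patients in the wards of the departments of neurology and rehabilitation medicine from December 2021 to December 2023 will be screened for eligibility". Methods 1(5), Recruitment, says "This trial aims to recruit 45 in- or outpatients with PSCI".

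**Allocation.** Methods 1(6), Randomization and blinding, says that "all eligible patients were equal assigned to one of nine active rTMS treatment group based on four rTMS parameters". No stratification factor is named. Methods 1(4), Sample size, gives "5 patients per group, 15 patients per stimulating site subgroup".

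**Analysis.** Section 4, Statistical analyses, applies range analysis and one-way ANOVA to MoCA-BJ, TMT, MBI, LIADL and SS-QOL. Range analysis is used to find the optimum combination. For the test, "The one-way ANOVA was used to determine the statistical significance in nine different" parameter combinations. No covariate appears. Clinical scores are taken at W0, W5 and W17 (Methods 1(3), Participant timeline).

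**The concern.** Patients at different distances from their stroke may be at different stages of recovery, and two patients with the same MoCA-BJ at W0 may have different courses over the next 5 to 17 weeks. All nine arms are active, so the main clinical product of the trial is a ranking of parameter levels. In its usual form, range analysis ranks raw level means with no error term. If one allocation happens to put earlier patients at one level, their recovery is credited to that setting. The same variation enlarges the residual term of the ANOVA.

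The criterion and the two setting statements also leave open how wide the range of time since stroke will be, and hence to which patients the named optimum applies.

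**Working it through.** **1. The plan's own figures.** 9 × 5 = 45 and 3 levels × 15 = 45, as stated. The protocol gives no SD, effect size or power to reproduce. The one-way ANOVA has 45 − 9 = 36 residual degrees of freedom. A main-effects model for four three-level factors uses the same 8 degrees of freedom between arms (4 × 2), so it also leaves 36.

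**2. What the criterion bounds.** Six months is attached to the interval from stroke to onset of the deficit, and three months to its duration. Entry is therefore at least about 3 months after stroke. On the literal reading there is no upper limit. If 6 months was meant as a limit on entry, the range is about 3 to 6 months.

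**3. Chance imbalance in any baseline covariate.** A standard normal covariate was allocated at random to the 45 places of Table 2 and level means were compared (results in covariate SD):

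- SD of the difference between two level means: √(2/15) = 0.37
- Mean gap between highest and lowest of three level means: 0.44
- Gap above 0.5 for a given factor: 36% of allocations
- Gap above 0.5 for at least one of the four factors: 83%
- Gap above 0.75 for at least one factor: 34%
- Mean of the largest of the four gaps: 0.69

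The group list below Table 2 differs from the table in six groups, but it is also orthogonal and gives the same figures.

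**4. What adjustment removes.** Let R² be the share of outcome variance that log time since stroke explains beyond the baseline score. It is not in the protocol; 0.05 to 0.20 is assumed. SD below means the outcome SD before log time is added. The variance ratio of a level contrast, with against without log time, is about (1 − R²) × (1 + 1/34), where 34 = 36 − 2. The mean largest chance gap with no true effect, 0.685 SD without log time, scales with its square root.

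| R² | Variance ratio | Mean largest gap |
|---|---|---|
| 0 | 1.03 | 0.70 SD |
| 0.05 | 0.95 × 1.029 = 0.98 | 0.68 SD |
| 0.10 | 0.90 × 1.029 = 0.93 | 0.66 SD |
| 0.20 | 0.80 × 1.029 = 0.82 | 0.62 SD |

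Simulation gave 1.03, 0.98, 0.93 and 0.82, and the same gaps. Adding a baseline term to both models left the ratios for log time unchanged.

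**5. Effect on the choice of level.** With one level truly better by 0.3 SD, it has the highest mean in 68% of simulated trials without log time, and in 68%, 69% or 71% with it (R² 0.05, 0.10, 0.20). With a true advantage of 0.5 SD, 86% becomes 86%, 87% or 89%.

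**6. Cost of two covariates.** The baseline score and log time together use two degrees of freedom (36 to 34). If both were unrelated to outcome, variance would rise by a factor of about 1 + 2/33 = 1.06, or about 3% each.

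**The case against.** **Random allocation keeps the comparison valid.** This stands. A reader might infer that the design favours one setting. It does not: no level is expected to receive earlier patients, and the F test is valid without the covariate.

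**The imbalance figures suggest more than adjustment delivers.** This also stands. At R² 0.10 to 0.20, a largest covariate gap of 0.685 SD corresponds to √R² × 0.685 = 0.22 to 0.31 outcome SD, and a reader might infer that adjustment removes that much spurious difference. It does not, because this part combines in quadrature with the remaining noise. At R² 0.10, √(0.22² + 0.65²) = 0.69, and removing the first term leaves about 0.65, or 0.66 after the cost of estimating the slope.

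**The link to outcome is assumed.** The protocol gives neither the spread of time since stroke nor its relation to MoCA-BJ or TMT. The same imbalance would arise for age or lesion type. This limits the size of the claim, but log time remains a reasonable choice: it bears on recovery during follow-up, and the event must be dated to apply the criterion.

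**The wide reading may not be intended.** A reader might infer that patients years after stroke will be enrolled. The wording does not exclude them, but the criterion summarises guidelines and may have been meant as a 3-to-6-month window. In that case the gain may be smaller.

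**Covariates can be left to an analysis plan.** That is often fair, but here the protocol names its analysis, and a one-way ANOVA has no place for a covariate.

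**Conclusion.** The point holds as a low-cost improvement to a stated analysis and as two wording problems. The entry criterion does not clearly limit time from stroke to entry, and the setting statements conflict; both need clarifying whatever R² is. Leaving time since stroke out of the analysis adds noise and chance imbalance, not bias. Under an assumed partial R² of 0.05 to 0.20, adjustment lowers the variance of a level contrast by about 2% to 18%, lowers the mean largest chance gap from about 0.69 to between 0.68 and 0.62 SD, and raises correct choice of a level better by 0.3 SD by about 0 to 4 percentage points. At R² 0 it costs about 3% in variance. No separate figure can be given for a 3-to-6-month window, because the protocol gives no distribution of time since stroke. Most of the risk of naming a chance winner comes from 15 patients per level and a ranking without an error term, which this change does not cure.

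**What to change.** - **Section 4, Statistical analyses:** replace the unadjusted analysis of MoCA-BJ, TMT, MBI, LIADL and SS-QOL with a pre-specified model containing the rTMS factors, the baseline score of that scale and log time from stroke to W0. Take the level means used to name the optimum from this model.
- **Methods 1(2), Eligibility criteria:** state whether 6 months limits entry to the trial or only onset of the deficit.
- **Methods 1(1) and 1(5):** reconcile ward patients with in- or outpatients.
- **Reporting:** tabulate time since stroke and care setting by arm.

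**Cost:** a few sentences of wording and two of 36 residual degrees of freedom, with about 3% more variance for each covariate that proves unrelated to outcome. The baseline score is already collected and dating the stroke is already part of judging eligibility, so little or no new data collection is needed.
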